### The Personalized Feedback Pamphlet ("Evaluate Your Drinking")

The "Evaluate Your Drinking" self-test pamphlet was modeled after the Drinker's Check-up [32,40,66] and the Fostering Self-Change intervention [33]. The pamphlet starts with an encouragement for the reader to evaluate his or her own drinking. The reader is then asked to record his or her drinking for each day of a typical week and to sum this information to calculate the number of drinks usually consumed per week (a 'standard drinks' chart is provided to help the reader). Next, information on the drinking patterns of males and females in the general Canadian population is provided. The reader is encouraged to compare his or her personal drinking to that of other Canadians and a graph is presented of the likelihood of adverse effects associated with different levels of consumption. The pamphlet concludes with a menu of options and encourages those readers who are concerned about their drinking to take the next step towards changing their alcohol consumption. Incorporated in this menu are low-risk drinking guidelines and a toll-free telephone number for individuals who would like to call to receive a free referral to a local treatment agency. To enhance impact and readability, the pamphlet was professionally produced in a multi-color, glossy format. The pamphlet was modeled after research-validated personalized feedback interventions and provides an easily completed normative feedback self-test for the reader in an attractive and eye-catching format [see Additional file 1].

### Control Condition Pamphlet ("Do You Know ... Alcohol")

The control pamphlet called 'Do you know .... Alcohol' is disseminated by the Centre for Addiction and Mental Health (CAMH). This pamphlet provides good quality information about alcohol, consequences of its misuse and safe drinking guidelines (same guidelines as are used in the personalized feedback pamphlet). The "Do you know" pamphlet is one of the most popular distributed by CAMH and is a high quality pamphlet that is a good example of educational materials disseminated about alcohol [see Additional file 2].

### Content of the Baseline Survey

(1) The Alcohol Use Disorders Identification Test will be used to measure level of alcohol consumption and severity of alcohol problems (a score of 8 or more on the AUDIT indicates a past 12 month alcohol problem) [64,65]. The AUDIT has been validated for use in telephone surveys [67]. Usual quantity of drinking will be assessed as a continuous variable. An additional item will ask the highest number of drinks the respondent recalled having on any one occasion in the past three months. Finally, respondents' drinking will also be assessed by asking the number of drinks consumed on each day of the last week.

(2) Six items assessing whether in the past 12 months alcohol had a harmful effect on respondents' (1) friendships/social life, (2) physical health, (3) outlook on life (happiness), (4) home life or marriage, (5) work, studies, or employment opportunities, or (6) financial position [68].

(3) Perceived drinking norms will be measured using a modified version of the Drinking Norms Rating Form [69]. Respondents will be asked how often they think a typical person their age and gender drinks and how often they consume five or more drinks on one occasion (same category response options as AUDIT). Further, respondents will be asked to estimate how much the typical person their age and gender usually drinks on one occasion.

(4) Perceived risk for drinking-related problems will be assessed using a six-item scale with questions about perceived vulnerability to harm from the drinkers' own perspectives [70].

(5) Following the procedure used by Neighbors [44], social reasons for drinking will be measured using the Social Rewards subscale of the Drinking Motives Questionnaire [63] a five item scale that asks respondents how often they are motivated to drink for positive social outcomes. Also, social outcomes expectancies and subjective evaluations of social effects of alcohol will be assessed using the sociability subscales of the Comprehensive Effects of Alcohol Scale [71].

(6) Formal addictions treatment utilization will be measured using a single item from the National Longitudinal Alcohol Epidemiological Survey [72]; "Have you ever gone anywhere or seen anyone for a reason that was related in any way to your drinking – a physician, counselor, Alcoholics Anonymous, or any other community agency or professional? Include help for combined alcohol and other drug use if alcohol was the major problem for which you sought help."

(7) A series of demographic characteristics will be assessed: age, gender, ethnicity, marital status, education, and employment status.

Problem drinkers (AUDIT score of 8 or more) will be recruited to participate in a three-month and a six-month follow-up telephone survey.

### Three-month Follow-up Survey

The three-month follow-up will occur roughly three-months after the intervention pamphlet is sent (or equivalent time for those in the control condition).

(1) Drinking in the last three months will be assessed using the same five items employed on the baseline survey, the first four framed for the past three months (frequency of consumption, drinks per occasion, frequency of 5+ consumption, highest number of drinks on one occasion) and the last asking how much the person drank on each day of the last week.

(2) Six items assessing whether in the past 3 months alcohol had a harmful effect on respondents' (1) friendships/social life, (2) physical health, (3) outlook on life (happiness), (4) home life or marriage, (5) work, studies, or employment opportunities, or (6) financial position [68].

(3) Mediator variables, perceived drinking norms and perceived risk will be measured using the same items as on the baseline survey.

(4) Formal addictions treatment utilization will be measured using the same single item as the baseline survey, modified to ask about the last three months.

### Six-month Follow-up Survey

(1) Using the same measures of alcohol consumption as the baseline survey, respondents' drinking over the time since the three-month follow-up will be assessed.

(2) The same six items assessing any harmful effects of alcohol in the past 3 months alcohol.

(3) Formal addictions treatment utilization will be measured using the same single item as the baseline survey, modified to ask about the last three months. In addition, respondents in the personalized feedback pamphlet condition will be asked if they called the telephone number provided on the pamphlet in order to assess whether the pamphlet stimulates additional help seeking.

(4) Knowledge of whether the household received any drinking-related materials will be assessed. Respondents will be asked if their household received either of the two pamphlets that were mailed. If they received one they will be asked which one and whether they read it. Those who received the "Evaluate Your Drinking" pamphlet and read it will be asked if the did the self-test contained in the pamphlet.

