**Methods/design:**

Problem drinkers recruited on a baseline population telephone survey conducted in a major metropolitan city in Canada will be randomized to one of three conditions – a personalized feedback pamphlet condition, a control pamphlet condition, or a no intervention control condition. In the week after the baseline survey, households in the two pamphlet conditions will be sent their respective pamphlets. Changes in drinking will be assessed post intervention at three-month and six-month follow-ups. Drinking outcomes will be compared between experimental conditions using Structural Equation Modeling. The primary hypothesis is that problem drinkers from households who receive the personalized feedback pamphlet intervention will display significantly improved drinking outcomes at three and six-month follow-ups as compared to problem drinkers from households in the no intervention control condition. Secondary hypotheses will test the impact of the intervention on help seeking, and explore the mediating or moderating role of perceived drinking norms, perceived alcohol risks and the problem drinker's social reasons for drinking.

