### Collateral Confirmation

At the six-month follow-up respondents will be asked to provide the name of a collateral to confirm their drinking self-reports. Collaterals identified for participation will be mailed a letter explaining that they have been nominated to act as a collateral. Collaterals will then be contacted by telephone to confirm their willingness to talk about the respondent's drinking. The 10-minute telephone interview will cover the respondent's drinking in the past three months and any use of treatment services for alcohol problems during the past three months (mirror items of the respondents' six-month follow-up survey). Collaterals will be offered a $20 honorarium for completing this interview.

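### The help-line call question is asked only in the feedback arm, so its count is descriptive and cannot show additional help seeking

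*Protocol article*

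**What the plan says.** The protocol article collects help seeking in two ways.

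- **Formal treatment use, all arms.** The Six-month Follow-up Survey states: "Formal addictions treatment utilization will be measured using the same single item as the baseline survey, modified to ask about the last three months". No arm restriction is attached. The same item is in the baseline survey and, for the past three months, in the Three-month Follow-up Survey. The baseline wording begins "Have you ever gone anywhere or seen anyone for a reason that was related in any way to your drinking" and goes on to name a physician, a counselor, a mutual-help group and other agencies or professionals. Under Collateral Confirmation, collaterals are asked about "any use of treatment services for alcohol problems during the past three months".
- **Calls to the pamphlet's number, one arm.** The same six-month item adds that "respondents in the personalized feedback pamphlet condition will be asked if they called the telephone number provided on the pamphlet", and gives the reason: "in order to assess whether the pamphlet stimulates additional help seeking". The three-month survey lists no such question.

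The description of the feedback pamphlet includes "a toll-free telephone number for individuals who would like to call to receive a free referral to a local treatment agency". The control pamphlet is described differently ("This pamphlet provides good quality information about alcohol, consequences of its misuse and safe drinking guidelines"), and no telephone number is mentioned for it.

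The abstract says: "Secondary hypotheses will test the impact of the intervention on help seeking". The six hypotheses listed under Aim concern drinking outcomes, two mediators and two moderators; none concerns help seeking.

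**The concern.** To say that a pamphlet stimulates additional help seeking is a causal and comparative statement. It needs to be known how many people would have called for help without the pamphlet, and in this trial only the control arms can supply that. They are not asked.

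Some feedback-arm callers might have called another line, or sought help in another way, had no pamphlet come. A count from one arm cannot separate those people from callers whom the pamphlet prompted. The all-arm item does not clearly fill the gap, because a call to a referral line is neither going somewhere nor seeing someone.

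At stake is part of a secondary question: the effect on the help-seeking step that the feedback pamphlet most directly invites. An analysis plan cannot repair this later, since answers not collected in the control arms cannot be recovered.

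**Working it through.** **1. What each item can support**

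| Measure | Arms asked | When | Randomised comparison? |
|---|---|---|---|
| Formal treatment use (respondent) | All three | Baseline, 3 and 6 months | Yes |
| Treatment use (collateral) | No arm restriction stated | After 6 months | Yes, among those with a collateral |
| Call to the pamphlet's number | Feedback only | 6 months | No |

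If a caller then attends the agency to which he or she was referred, the all-arm item should record it. A call with no later contact is not clearly recorded for anyone outside the feedback arm.

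**2. The plan's own figure (context only)**

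The article gives no figure for help seeking. Its sample size is for drinking: f = 0.10, 80% power, .05 level, 390 per condition. With two groups, f = 0.10 is d = 0.20. Taking a two-sided test, n = 2 × (1.96 + 0.84)² / 0.20² gives 393 per arm when computed without rounding. This reproduces the stated 390 to within 1%; power at 390 is 79.8%. It has no bearing on which arms are asked about calls.

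**3. What the all-arm treatment item can detect**

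With 390 per arm, two-sided .05 and 80% power, a two-proportion comparison detects the following. The control rates are assumptions, as the article gives none.

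- 2% against about 6.0%
- 5% against about 10.4%
- 10% against about 16.9%

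So a comparison exists, but only for fairly large differences.

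**4. What asking all arms about calls would add**

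- Respondents per arm at six months: 1830 recruited × 0.80 follow-up / 3 = 488.
- Half-width of the 95% interval for a difference, with rate p in both arms: 1.96 × √(2p(1 − p)/488).
- p = 3% (assumed): √(2 × 0.03 × 0.97/488) = 0.0109; × 1.96 = 2.1 points.
- p = 1%: √(2 × 0.01 × 0.99/488) = 0.0064; × 1.96 = 1.2 points.
- p = 5%: √(2 × 0.05 × 0.95/488) = 0.0140; × 1.96 = 2.7 points.

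As planned, 3% of feedback respondents reporting a call would be compatible with anything from 0 to 3 points being due to the pamphlet, and the data could not narrow that range. With all arms asked, the difference can be estimated.

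The precision is modest. If half of a 3% rate were due to the pamphlet (3% against 1.5%), the pooled standard error is √(2 × 0.0225 × 0.9775/488) = 0.0095. The ratio is 0.015/0.0095 = 1.58, and power is about 35%.

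**The case against.** The best defence is that the call question is an add-on about use of the pamphlet, not the test of help seeking. It follows the all-arm treatment item and concerns a number that, as described, only the feedback pamphlet carries. It could not be put in that form to people who were sent no pamphlet. The outcome that matters, contact with an agency or professional, is asked in every arm. An extra all-arm item would also settle little: about 35% power in the example above.

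Much of this stands. A reader might infer that the trial has no comparator for help seeking at all, and the article does not support that: formal treatment use is compared by randomised arm at both follow-ups.

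A reader might also infer that the arm-specific question harms the six-month interview by revealing allocation. That is not supported either. The next item already asks respondents which pamphlet their household received, and the drinking and harm items are listed before both. The article as shown makes no claim of interviewer masking.

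The stated purpose of the call question is what the defence does not answer. The article ties a claim about an increase to a measure taken in one arm. A neutral question about any help line avoids the objection about the pamphlet's number, and the following item on pamphlet receipt already uses the same branching form. Low power limits what can be learned, but an imprecise randomised difference is still interpretable in a way that a one-arm count is not.

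**Conclusion.** The point holds for help-line calls only. The call count describes use of the pamphlet's number and cannot, by itself, show additional help seeking. The all-arm treatment item supports a randomised test of formal help seeking but does not clearly cover a call.

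Severity is minor. This is a secondary measure; the primary hypothesis, the sample size and the drinking outcomes do not depend on it. The size given (0 to 3 points unresolved, against an interval of about ±2.1 points if all arms are asked) rests on an assumed 3% call rate and on the article's 80% six-month follow-up, split equally over three arms. It also takes the pamphlet not to reduce calling. Rates of 1% to 5% give half-widths of about 1.2 to 2.7 points.

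The absence of help seeking from the hypotheses under Aim, although the abstract promises a test, is a related but separate inconsistency.

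**What to change.** At both follow-ups, after the drinking items, ask respondents in all three arms one neutral question: whether they called any alcohol help or referral line in the past three months. Compare it by randomised arm beside the treatment-use item, and name the two together as the secondary help-seeking outcome, which would also bring the Aim into line with the abstract. Keep the question about the pamphlet's number as a follow-on for those who report a call.

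If the question is not added, state that the call count is descriptive, remove the purpose of assessing additional help seeking from it, and rest the help-seeking test on the all-arm treatment item.

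The cost is a few seconds in interviews that are already being made. The limitation is modest precision for a rare event, so the result should be reported as an estimate with its interval.

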### Collateral Confirmation

At the six-month follow-up respondents will be asked to provide the name of a collateral to confirm their drinking self-reports. Collaterals identified for participation will be mailed a letter explaining that they have been nominated to act as a collateral. Collaterals will then be contacted by telephone to confirm their willingness to talk about the respondent's drinking. The 10-minute telephone interview will cover the respondent's drinking in the past three months and any use of treatment services for alcohol problems during the past three months (mirror items of the respondents' six-month follow-up survey). Collaterals will be offered a $20 honorarium for completing this interview.

### Data Analysis

#### Power Analyses

The power analysis conducted to estimate the sample size required to test the hypotheses of this study used the procedures suggested by Cohen [73] for estimating statistical significance. That is, what is the sample size required to detect an increase in the variance explained due to the inclusion of the personalized feedback pamphlet intervention into the model (Hypothesis 1)? Based on pilot study results, a 1% increase in explained variance can be expected (a small effect size of f = 0.10; note – corresponded to a reduction of two drinks per week in the pilot study). Following the convention that studies should be designed to have a statistical power of at least 80%, and that hypotheses be tested at the .05 level of significance, SamplePower 1.0 [74] was used to estimate the required sample size. These specifications resulted in a final sample (required after attrition) of N = 390 in each condition (N = 1170 total). Given that the inclusion of perceived risk as a moderator resulted in an increase in explained variance of 9% (also in the pilot test), this same sample size would result in a power of better than 99% to test for the mediator and moderator hypotheses (assuming a similar effect size). Results presented by Neighbors and colleagues [44] found similar effect sizes for the mediator hypothesis regarding perceived drinking norms and the moderator hypothesis regarding drinking for social reasons, indicating that the proposed sample size will be adequate to test these hypotheses as well.

Although Structural Equation Modeling [75], the analysis method to be used, allows for the sophisticated treatment of missing data, it is still important to assure an adequate number of respondents are followed-up. Based on previous experience [76], it is estimated that 80% of respondents will be followed-up on the six-month follow-up. This means that about 1830 respondents who agree to the follow-up will need to be recruited on the baseline survey in order to account for respondent attrition. We are assuming a worst-case scenario of an 80% follow-up rate on each of the three-month and six-month follow-up interviews but that the 20% lost on each follow-up survey will be different respondents. Thus, to obtain 1170 respondents with complete follow-up data, a follow-up rate of 80% × 80% = 64% is assumed. Given that previous research [77] has indicated that 75% of problem drinkers will agree to be followed-up, the baseline survey will need to include 2440 respondents who are problem drinkers (AUDIT score of 8 or more). As 20% of the baseline sample will be problem drinkers, the full baseline survey will need to screen 12200 respondents who consume alcohol at least once per month (based on previous experience, 20% of monthly alcohol drinkers have an AUDIT score of 8 or more). This will allow a final sample size of 1170 problem drinkers participating in the six-month follow-up. In summary, from 12,200 respondents interviewed at baseline 20% (n = 2440) will be problem drinkers, 75% of whom (n = 1830) will agree to participate in the follow-up interviews, and an 80% follow-up rate for each follow-up survey will give total data for 1170 respondents.

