### Does Perceived Risk Mediate the Effects of Safe Drinking Interventions?

The motivational impact of perceived risk is clearly shown by considering four cognitive theories of health protective behavior. In particular, the health belief model [55], protection motivation theory [56], the theory of reasoned action [57], and subjective expected utility theory [58] are all identical insofar as they each assume "that anticipation of a negative health outcome and the desire to avoid this outcome or reduce its impact creates motivation for self-protection" [p. 234, [59]]. We have also conducted correlational research exploring why some drinkers perceive risk associated with their drinking while others do not. These studies concluded that there is a need to consider perceived risk as well as objective problem status when designing and evaluating interventions to help heavy drinkers [60]. One of the studies described in the Preliminary Studies section below also indicates the mediating role that perceived risk may play in drinkers' reactions to safe drinking interventions [39].

Why might perceived risk mediate the impact of personalized feedback interventions? As was discussed earlier, such interventions provide normative feedback to respondents, comparing their drinking to others in the general population. As many heavy drinkers overestimate how much others drink, this normative information often comes as a surprise to them, allowing them to make the social comparison that they drink more than others [34]. According to cognitive theories of health protective behavior, this information leads to changes in health behavior because it results in an increase in respondents' perceived vulnerability. The recipient recognizes that he or she is engaged in a risky health behavior (i.e., drinking more than others). This increase in perceived risk then motivates respondents to reduce their drinking. The current study will test whether changes in perceived risk mediate reductions in drinking. Although not necessarily contradictory, the mediator hypotheses of perceived drinking norms and of perceived risk come from different theories of change. This study will measure both these constructs and evaluate their validity as potential mediators of the impact of personalized feedback interventions. Secondary analyses will also explore the possible interrelationship between perceived risk and drinking norms as hypothesized mediators of the impact of the ultra-brief intervention.

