The results of this trial indicated that perceived risk might act as either a mediator or a moderator of respondents' reactions to safe drinking interventions. This finding is important to confirm because it points to one of the factors that may differentiate those who continue problem drinking from those who reduce their drinking. However, the post-test only design employed in this research did not allow causal statements to be made regarding the effects of respondents' perceived risk because this variable, along with all others, was assessed after the intervention was administered. Thus, there was no way of knowing whether those with greater perceived risk about alcohol consumption at the one-month follow-up experienced an increase in their perceived risk after receiving the intervention or had higher perceived risk scores already at baseline. To address this issue, the current study will conduct an appropriate evaluation of the role of perceived risk, assessing it at baseline as well as at the three-month follow-up, and then evaluating the potential mediating or moderating effect of perceived risk on problem drinkers' drinking outcomes at six-month follow-up.

It is also important to conduct an appropriate evaluation of the role of perceived risk because of the possibility indicated in this pilot study that respondents with no perceived risk might react negatively to receiving the pamphlet. This post-test only pilot study can only be taken as the most preliminary of evidence that those respondents without any perceived vulnerability with respect to their drinking might react negatively to the pamphlet by drinking more. However, we feel that the possible 'boomerang' effect of this ultra-brief intervention among problem drinkers with no perceived risk is an important one to investigate. This is because confirmation of this pattern of results would indicate the need to target interventions, such as this normative feedback pamphlet, to problem drinkers who are concerned about their drinking. Thus, we feel that the potential benefits of conducting this test outweigh the ethical risks associated with conducting a trial where there is the potential of a small negative impact among some participants.

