#### Rationale for the choice of study design

Why do we believe that the proposed study design is the best for testing the impact of this personalized feedback pamphlet? The intent of this project is to evaluate an ultra-brief intervention for problem drinkers that can be used in public health initiatives. As such, it is important that the intervention pamphlet be evaluated in a setting that mimics how it will be used. Thus, the pamphlets will be sent addressed to the household rather than addressed to the respondents because public health initiatives are often non-specific in their target recipients. The proposed research design has the advantage of allowing the pamphlet to be sent to all households in the intervention condition, irrespective of whether any of the respondents are specifically interested in receiving self-help materials. In order to conduct a study where intervention materials are sent directly to the person by name, for ethical reasons the respondent must at least state that he or she is hypothetically interested in receiving such materials. A study in which materials are sent unsolicited to households has been judged ethical because receiving such materials unsolicited (and unaddressed to a specific individual) is not an unusual occurrence given that public health initiatives are ongoing in the Toronto metropolitan area. However, informed consent is given because all respondents are told about the possibility of their household receiving the pamphlet. Further, it is important to be able to send materials to all households because interest in self-help materials covaries with respondents' perceived risk. In the pilot study described above, 76% of problem drinkers who perceived no risk associated with their drinking were not interested in self-help materials. This group comprised 32% of all problem drinkers in the sample. Thus, although the proposed method reduces the power of the intervention because not all respondents will see the pamphlet, it is still the best design for our purposes because it allows recruiting some problem drinkers with no perceived risk regarding their alcohol consumption. Studying the reactions of problem drinkers who do not perceive any risk associated with their drinking to intervention materials is of great importance because results from the pilot study for this proposal (Study 1 in the preliminary studies section) indicated that this group could react to the intervention materials by drinking more. Although the results of Study 1 were not conclusive because of its post-test only design and the fact that this 'boomerang' effect in reaction to the materials was a trend rather than a statistically significant result, we feel that the study of these types of unintentional effects is essential. The personalized feedback pamphlet is intended for wide distribution in the general public. If we confirm that this ultra-brief intervention can have a negative impact on some sub-groups of problem drinkers then this finding would speak to the need to target the intervention to only those drinkers who already voice some concern regarding their drinking. As there is insufficient evidence to-date that could confirm or refute this hypothesis, we feel that the need to test this hypothesis appropriately outweighs the potential ethical dilemma of causing a small unintended increase in alcohol consumption among a population of drinkers who are not seeking treatment and who meet criteria for a rather liberal definition of problem drinking (AUDIT score of 8 or more).

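### The power of better than 99% given for the mediator hypotheses comes from a moderator effect in a post-test-only pilot, so it is not supported as power to test mediation, most clearly for perceived risk (H4)

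*Protocol article*

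**What the plan says.** The Power Analyses section sizes the trial on H1. It states that "a 1% increase in explained variance can be expected (a small effect size of f = 0.10", asks that "hypotheses be tested at the .05 level of significance", and applies the convention that "studies should be designed to have a statistical power of at least 80" per cent. The result is 390 per condition after attrition, 1170 in all.

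It then turns to the other hypotheses: "Given that the inclusion of perceived risk as a moderator resulted in an increase in explained variance of 9" per cent in the pilot, "this same sample size would result in a power of better than 99% to test for the mediator and moderator hypotheses". A short proviso makes this conditional on the effect being of similar size. The next sentence cites a separate normative-feedback study as having found similar effects for the norms mediator (H3) and the social-reasons moderator (H6). It prints no figure from that study.

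Three other places bear on this:

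- **Preliminary Study # 1.** The pilot measured everything after the pamphlet. The article says there was no way to tell whether people with higher perceived risk had "experienced an increase in their perceived risk after receiving the intervention or had higher perceived risk scores already at baseline".
- **Does Perceived Risk Mediate the Effects of Safe Drinking Interventions?** "The current study will test whether changes in perceived risk mediate reductions in drinking".
- **Aim.** H3 and H4 are labelled mediator hypotheses. They are worded as comparisons among people who receive the intervention: those whose norms or perceived risk changed by three months against those whose did not, with drinking at six months as the outcome.

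**The concern.** A mediation claim has two links. The pamphlet must change the mediator (path a), and the change must predict later drinking (path b). A gain in explained variance from entering perceived risk as a moderator measures neither. It describes how the pamphlet's association with drinking varies with perceived risk. The pilot had no baseline measure of perceived risk, and the article reports no pamphlet effect on it from that study, so path a for H4 has no reported estimate.

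The article presents H3 and H4 as tests of two theories of why the feedback works. If power is printed as near certain, a null result could be taken as good evidence that norms or perceived risk are not the mechanism. The printed figure gives no basis for that reading.

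**Working it through.** **Inputs from the Power Analyses section:** alpha .05 (sidedness not stated), H1 increment 1%, pilot moderator increment 9%, 390 per condition. **Not in the article:** any pamphlet effect on either mediator, and any effect of mediator change on drinking. Values for these below are assumptions, shown as ranges.

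**1. Reproduce the plan's figures.** For a 1-df increment the noncentral F has λ = N·R²/(1 − R²).

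- H1, two arms, N = 780: λ = 780 × 0.01/0.99 = 7.88, power 80.1%. The smallest N for 80% is 779, about 390 per arm. Two-sided .05 therefore reproduces the plan; a one-sided test would give 310 per arm.
- 9% increment at N = 390: λ = 390 × 0.09/0.91 = 38.6, power over 99.9%. It is higher still at N = 780 and 1170. The printed 99% is correct for a 9% increment.

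**2. Test of the indirect effect, pamphlet v one control arm (390 v 390).** The joint-significance test rejects only if both paths are significant, so power ≈ power(a) × power(b), which cannot exceed power(a). With path b at 9%, power(b) is practically 1 and path a decides. For two equal arms R² = d²/(d² + 4), so d = 0.20 gives 0.04/4.04 = 0.99%.

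| Mediator variance explained by pamphlet | Ceiling on power |
|---|---|
| 0.25% (d about 0.10) | 29% |
| 0.5% | 51% |
| 1% (d about 0.20) | 80% |
| 2% | 98% |
| 2.3% (d about 0.31) | 99% |

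A simulation (3000 runs, path b 9%, no direct effect) at d = 0.20 gave 80.2% for joint significance and 78.3% for the Sobel test. With both control arms pooled (390 v 780), the ceiling at d = 0.20 is about 90%.

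**3. What the plan's expected effect on drinking would imply.** A 1% effect is a standardised 0.10. If a share s of it runs through one mediator, a = s × 0.10/b.

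- s = 1, b = 0.3: a = 0.333, R² = 11.1%, power over 99%. Power stays over 99% for b from 0.2 to 0.5.
- s = 0.5: over 99% at b = 0.2, 99.7% at 0.3, 94% at 0.4, 80% at 0.5.
- s = 0.25: 94%, 65%, 42% and 29% at the same values of b.

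**4. H3 and H4 as worded in the Aim section (within the pamphlet arm, n = 390).** Path a is not tested, so the ceiling does not apply. If mediator change explains 9% of six-month drinking, power is over 99.9%. If it explains 1%, λ = 390 × 0.01/0.99 = 3.94 and power is 51%.

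**The case against.** The strongest reply has four parts.

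- **The sentence is conditional.** It assumes a similar effect size, and the arithmetic then follows. That stands against any charge of miscalculation. It does not supply the missing input: similarity of size does not turn a moderator effect into an effect of the pamphlet on the mediator.
- **H3 and H4 as worded are within-arm comparisons**, so the path-a ceiling does not bind. This stands. But the predictor is change from baseline to three months, which the pilot did not measure, so 9% is unsupported here too. The comparison is also not randomised, and so is not in itself a test of mediation.
- **H3 has its own citation.** This stands in part. The study is not available here and no effect size is printed, so its support can be neither confirmed nor dismissed. The article describes its sample as college students, and says of its own household mailing that "the proposed method reduces the power of the intervention because not all respondents will see the pamphlet". How far that would reduce an arm-wide effect on norms cannot be worked out from the article.
- **The mediator questions are secondary** and do not drive the sample size. True, and it limits the consequence to interpretation.

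A reader might go further and infer that mediation power is really 80%, or that the trial is underpowered for mediation. The article supports neither. Its 1% is the expected effect on drinking, not on a mediator, and step 3 shows that power over 99% is reachable under full mediation and under some partial mediation.

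**Conclusion.** The concern holds as an unsupported basis for a printed power figure, not as an arithmetic error. It is clearest for H4, where the only source is a pilot that the article itself says could not show a rise in perceived risk. For H3 the power cannot be checked either way.

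Power for the mediator hypotheses is conditional on effects the article does not give. For an indirect-effect test with 390 v 390, the ceiling runs from 29% to 99% as the pamphlet's share of mediator variance goes from 0.25% to about 2.3%. Within the pamphlet arm, power is 51% at 1% and over 99% at 9%.

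These results assume two-sided .05, 390 analysed per arm, and percentages that refer to mediator variance after any baseline adjustment the model makes. The choice of test is also an assumption, since the article names structural equation modelling without specifying the mediation test. No fault in the sample size for H1 follows, and the point takes no view on whether 9% is a sound input for the moderator hypotheses.

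**What to change.** In the Power Analyses section, limit the figure of better than 99% to the perceived-risk moderator hypothesis (H5) from which it was derived. For H3 and H4, name the test and the arms compared, and give power conditionally on a stated pamphlet-to-mediator effect and a stated mediator-to-drinking effect. For example:

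> For a test of the indirect effect comparing the feedback pamphlet with no intervention (390 v 390, two-sided .05), power is at most about 80% if the pamphlet shifts the mediator by d = 0.20 and 99% at d = 0.31. No estimate of this effect on perceived risk is reported from the pilot.

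For H3, print the effect size taken from the cited study, or say that none is assumed. Add that a non-significant indirect effect will be reported with its confidence interval and not as evidence against the mechanism.

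The cost is wording and a less favourable printed figure. Sample size, data collection and analysis method are unchanged.
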